## 7. STUDY POPULATION

### 7.1 RECRUITMENT PROCEDURE

Where possible, an informed written consent will be obtained from the parent in the antenatal period. For antenatal consenting, pregnant women considered at risk of delivering before 29 weeks gestation will be approached by the research team member or a clinical team member (trained medical personnel such as neonatal fellow/registrar/consultant) who will introduce the trial to parents and provide a participant information sheet. Parents will then be able to have an informed discussion with the Research team member or clinical team member who will obtain written consent from those willing to participate in the trial. For participants where antenatal consent was obtained, randomisation will occur after birth of the child if study inclusion criteria are met.

Often premature infants deliver without much time for consent, and at times, as an emergency delivery. If there was no opportunity to obtain antenatal consent, , instead of postnatal consenting within 6 hours of birth, a waiver of consent has been approved for enrolment of the baby and consent for continued participation will be obtained in first 5 days after birth of the baby by the research team member or a clinical team member (trained medical personnel such as neonatal fellow/registrar/consultant).

### 7.2 INCLUSION CRITERIA

- Preterm infants (singleton or twins births) <29 weeks gestation who are either inborn (born at the local study site hospital) or outborn (born outside the local study site hospital) and less than 6 hours of age when admitted to the study site NICU.

### 7.3 EXCLUSION CRITERIA

- Infants admitted to NICU beyond 6 hours of age.
- Infants with an antenatal or postnatal diagnosis of major congenital anomaly requiring major surgery or a genetic disorder associated with neurological impairment.
- Multiple births beyond twins are excluded for practical reasons (sites may not have additional NIRS monitors and the rates of multiple births beyond twins in Australia and New Zealand is very low < 2%).

## 7.4 CONSENT

Recruitment of participants will occur after obtaining an informed written consent. Where possible, an informed written consent will be obtained from the parent in the antenatal period. Where antenatal consent could not be obtained, instead of postnatal consenting within 6 hours of birth, a waiver of consent has been approved for enrolment of the baby. Families will be approached within the first five days after birth and consent will be obtained prior to the use of data.

Explicit consent will be obtained prior to any data being used and if consent has not been obtained then the data will not be used.

### Participant who are randomised but cannot be approached for consent

We anticipate a small number of participants in the study for whom it is not possible to obtain consent after randomisation. This may occur due to death of the baby, or the development of a life-threatening complication. Due to the stressful nature of their baby's illness, the parents will not be in a state to provide consent and it is inappropriate to discuss information on consent with grieving parents. In such instances, no attempt will be made to contact the parents for a consent and all data collected so far be removed from the study. Should grieving parents accept continuation of intensive care treatment, then contact will be made with the parents when they are in a state of being approached for consent.

Additionally, if parent/s have COVID-19 infection at the time of delivery or in the first 5 days following the birth of the baby, they are very stressed and are in isolation for several days. These parents are not in a state to provide consent and it is inappropriate to discuss information on consent. In such instances, contact will be made with the parents when they are in a state of being approached for consent, which will usually be beyond 5 days of age.

The provision of study information may occur by email followed by a phone conversation or video conferencing with the family to facilitate timely consenting.

## 8. PARTICIPANT SAFETY AND WITHDRAWAL

### 8.1 RISK MANAGEMENT AND SAFETY

NIRS monitors have Therapeutic Goods Administration approval (for Australian sites) and Food and Drug administration approval (for US sites).

Regular skin surveillance as per local unit practice will be conducted to check the skin health from NIRS sensor placement. In our experience, when using non-adhesive NIRS sensors, skin irritation is very rare and is temporary in nature, does not require treatment and using current clinical practice (such as no tight bandages etc. use) is highly unlikely to cause any clinically relevant problems.

As a standard practice local hospital social worker routinely provide counselling to parents of premature babies. Further sessions can be offered to families who are participating in the clinical trial if needed.

### 8.2 ADVERSE EVENT REPORTING

**Serious adverse event:** any adverse event that results in death, is life-threatening, requires prolongation of existing hospitalisation, result in persistent or significant disability or incapacity, or requires intervention to prevent permanent impairment or damage.

**Below is a list of expected serious adverse events in premature babies born at this gestational age:**

- Death before hospital discharge
- Serious early and/ late onset sepsis
- Major intra-ventricular haemorrhage
- Neonatal chronic lung disease
- Pulmonary air leaks
- Advanced necrotising enterocolitis
- Peri-ventricular leukomalacia (PVL) or diffuse white matter loss
- Advanced retinopathy of prematurity
- Sensorineural hearing loss
- Cerebral palsy
- Moderate to severe functional impairment.

Serious adverse events which may be life threatening are common in preterm infants, however, the proportion of **unexpected serious adverse events** (in the opinion of the investigator) is expected to be small.

AN **UNEXPECTED SERIOUS ADVERSE EVENT**(SAE) is any untoward medical occurrence that is not expected and:

- results in death, or
- is life-threatening (i.e. the subject is at risk of death at the time of the event), or
- requires prolongation of hospitalisation, or
- results in persistent or significant disability or incapacity

or

- other important medical events which, in the opinion of the investigator, are likely to become serious if untreated

NOTE: The term “life-threatening” in the definition of “serious” refers to an event in which the baby was at risk of death at the time of the event; it does not refer to an event which hypothetically might have caused death if it were more severe.

**The investigator is responsible for reporting all Unexpected Serious Adverse Events occurring during the study to the CI’s within 1 working day by email.** The Trial Management Committee (TMC) all other Principal Investigators participating in the study will be informed. The investigator or delegate at each participating institution is responsible for reporting unexpected serious adverse events to their HREC.

An independent Data Safety and Management Committee (DSMC) will be established, the DSMC will monitor the progress of all aspects of the study and will ensure that the study meets the highest standards of ethics and patient safety. It will review interim data and other emerging evidence, including relevant RCTs and overviews of RCTs. The DSMC will advise the TMC if in their view there is proof beyond reasonable doubt of net clinical benefit or harm, for all infants or for a subset of infants, that might reasonably be expected to influence the management of many clinicians. Data on key study outcomes will be monitored every 12 months, or more frequently if requested by the DSMC, to ensure safety. A charter will be written and agreed upon by TMC and DSMC for stopping the study prematurely, monitoring the trial more frequently or modifying the trial design.

### 8.3 HANDLING OF WITHDRAWALS

Parents that wish to withdraw their child's participation from the trial may do so at any stage of the study, without giving a reason and without any change to any aspect of treatment or relationship with the treating medical team. Parents of any child who is withdrawn from the study after randomisation and before or after the intervention is administered will be asked to allow collection of de-identified data. In our experience, based on currently ongoing and past prospective studies, participants withdrawing after providing consent is extremely uncommon.

### 8.4 REPLACEMENTS

Withdrawn participants will be replaced in the study. In Australia, New Zealand and other participating centres, a good neuro-developmental follow up exists as a standard practice where children born this young, are routinely followed up for 5 years and their developmental assessment is performed. To facilitate and ensure good long term follow up, existing measures which are standard practices includes providing appointment letters by post, reminding and confirming with families by phone and/or text message when follow up appointment is close to date.

## 9. STATISTICAL METHODS

### 9.1 SAMPLE SIZE ESTIMATION & JUSTIFICATION

A 50% reduction in mean burden of hypoxia and hyperoxia in active treatment relative to control would be considered worthwhile. This corresponds to a reduction of 0.3 in the mean of log-transformed burden. In the Safe BoosC II study (BoosC results) a 58% reduction was achieved. Assuming a standard deviation of 0.5 in log-transformed burden (Ref – BoosC protocol), this would require 45 babies per group to achieve 80% power at 5% two-sided alpha. To account for the clustering effect of twins being allocated to the same treatment, we assume that 30% of babies are twins (giving an average cluster size of 1.3, and a within-twin correlation of 0.1 in the outcome. This gives a design effect of 1.03 by which the sample size is adjusted, leading to a sample size of 47 per group, 94 babies in total. We aim to recruit 100 babies to account for some loss to follow-up or missing data.

### 9.2 POWER CALCULATIONS

See above

### 9.3 STATISTICAL METHODS TO BE UNDERTAKEN

Participant demographic and clinical characteristics and study outcomes will be presented using standard descriptive statistics: frequencies and percentages for categorical variables, mean, standard deviation and range or median, quartiles and range for continuous variables and the Kaplan-Meier method for time to event variables.

All efficacy analyses will be performed according to randomized treatment. The primary outcome of the log-transformed burden of hypoxia will be compared using generalized estimating equation methods with a normal distribution of the outcome and allowing for correlation between twins. The reduction in mean log-transformed burden and its 95% confidence limits will be back-transformed to calculate percentage reduction in mean burden and its confidence interval.

Other study outcomes will be compared using similar methods, using GEE methods with normal or binary outcome distribution and correlation between outcomes in twins. Adjusted models will explore predictors out outcomes. A detailed statistical analysis plan will be prepared prior to unblinding of study results.

## **10. STORAGE OF BLOOD AND TISSUE SAMPLES**

### **10.1 DETAILS OF WHERE SAMPLES WILL BE STORED, AND THE TYPE OF CONSENT FOR FUTURE USE OF SAMPLES**

Not applicable as blood and tissue samples are not collected for this study.

## **11. DATA SECURITY & HANDLING**

### **11.1 DETAILS OF WHERE RECORDS WILL BE KEPT & HOW LONG WILL THEY BE STORED**

Local data for local participants will be stored with local PI's

Central team (CI's, trial coordinator) will have access to de-identified data for all participants.

Data will be stored for a minimum of 15 years or until the youngest participant turns 25 (whichever is the longest).

### **11.2 CONFIDENTIALITY AND SECURITY**

The study will be conducted in accordance with applicable Privacy Acts and Regulations. All data generated in this study will remain confidential. All consent forms and identifiable information will be stored in a separate, locked filing cabinet or as per local PI's arrangement. Data collected at each study site will be coded and stored in a locked filing cabinet and electronically (password protected) as per local site security arrangements. All measurable steps will be taken to ensure that health information collected is protected at all times. Any identification codes will be stored in a different place from the data records to which they are linked. Data management will comply with relevant privacy protocols, such as The Australian Standard on personal privacy protection.

REDCap will maintain a list of participants enrolled. Each site PI will have access only to their site records. The three chief investigators and one clinical trial coordinator will have access to all sites de-identified data to oversee enrollment. Participants will be given unique codes to protect their identity on all documentation utilised for recording and analysis purposes. Separate data records will be maintained for identifiable and de-identified data. Site PI will be responsible for collating and maintaining local site data. For each site, the local PI or research team will download continuous data such as NIRS, physiological (peripheral oxygen saturation, heart rate) data and store it electronically using password protection on work computers. Each participant will be coded based on the centre. This data will be downloaded using SenSmart™ data management software into a CSV format which will then be exported to a statistical software for data analysis. Cranial ultrasounds and MRI brain (when performed) will be de-identified (where possible) and transferred electronically for central reporting by the Neuro-radiologists. This data will remain

with the Neuro-Radiologist securely at The Children's Hospital at Westmead, Radiology Department. All data files (de-identified) will be emailed to the CI's using work emails only. Motor performance videos will be transferred for centralised scoring using Accellion Secure File Transfer endorsed by NSW Health.

Following completion of this trial, a larger study is being planned. TMC and DMSC will consider if participant information can be used for the larger trial if there is no major change to study methodology.

Secure data disposal: After completion of the storage period, paper-based records will be disposed of securely in the respective institution's confidential disposal bins (red bins in NSW). All electronically stored data will be permanently deleted.

### 11.3 ANCILLARY DATA

Short videos (2-3 minutes long) are routinely collected to perform motor performance testing as part of routine developmental follow up. This will be kept as per local PI's arrangement in workplace computer that is password protected. Local PI will maintain record of this video (coded) and transfer using a secure electronic file transfer system approved by NSW Health Department or local health authority (such as Accellion Secure File Transfer). After the central reporting team has performed motor performance reporting, the de-identified video will be deleted by the central reporting team. Local PI will continue to retain a copy for medical records.

## 12. APPENDIX

### List of Attachments included:

| Document Name                     | Version Number | Date (e.g., 18 January 2012) |
|-----------------------------------|----------------|------------------------------|
| Picture of NIRS sensor on manikin | 1              | 25/10/2020                   |

## **STUDY SYNOPSIS**

The NIRTURE trial is a phase II single-blinded RCT with two parallel groups with 1:1 allocation stratified for site and gestational age (<26 weeks and  $\geq 26^{+0}$ – $28^{+6}$  weeks' gestation) addressing the following question: In premature babies (< 29 weeks gestation at birth), can dedicated treatment with cerebral oxygenation monitoring compared to usual treatment with blinded cerebral oxygenation monitoring, reduce the burden of cerebral hypoxia and hyperoxia in the first 5 days? The trial will use a neonatal population specific sensor and near infrared spectroscopy device from a single manufacturer.

Study design

[figure not shown]

## **STUDY OBJECTIVES**

### *Primary Objectives*

In premature babies (< 29 weeks gestation at birth), can a dedicated treatment with cerebral oxygenation monitoring compared to usual treatment, reduce the burden of cerebral hypoxia and hyperoxia in the first 5 days?

We hypothesise that the burden of hypoxia and hyperoxia can be reduced (by half) by a combination of specific treatment guideline and keeping cerebral oxygenation in the specific range of 65-90%.

### *Secondary Objectives*

To explore the relationship between cerebral hypoxia and hyperoxia in the first 5 days and the following:

- Mortality before hospital discharge.
- Brain injury before hospital discharge.
- Neonatal morbidities (chronic lung disease, necrotizing enterocolitis, retinopathy of prematurity) before hospital discharge.
- Neuro-developmental outcomes until 5 years of age.
- Physiological functions (heart rate, pulse oximetry, blood pressure) in the first 5 days.
- Physiological functions (observation of pulse oximetry) at 36-37 weeks PMA.
- Sleep architecture (based on sleep study) at 36-37 weeks PMA.

## **PATIENT POPULATION**

### *Inclusion criteria*

- Preterm infants (singleton or twin births) <29 weeks gestation who are either inborn (born at the local study site hospital) or outborn (born outside the local study site hospital) and less than 6 hours of age when admitted to the study site NICU.

### *Exclusion criteria*

- Infants admitted to NICU beyond 6 hours of age.
- Infants with an antenatal or postnatal diagnosis of major congenital anomaly requiring major surgery or a genetic disorder associated with neurological impairment.
- Multiple births beyond twins are excluded for practical reasons (sites may not have additional NIRS monitors and the rates of multiple births beyond twins in Australia and New Zealand is very low < 2%).

## **OUTCOMES**

### *Primary outcome*

- The burden of cerebral hypoxia and hyperoxia during the first 5 days expressed as percent hours.

### *Secondary outcomes*

- Newborn mortality rates prior to home discharge
- Brain injury based on cerebral imaging prior to home discharge
- Neonatal morbidities (chronic lung disease, necrotizing enterocolitis, retinopathy of prematurity) prior to home discharge

- Physiological functions (observation of pulse oximetry) at 36-37 weeks PMA.
- Sleep architecture (based on sleep study) at 36-37 weeks PMA.
- Motor performance assessment (General movements assessment) during NICU stay and at 4 months corrected age follow up.
- Neuro-developmental outcomes until 5 years of age.
- Measurement of physiological functions (heart rate, pulse oximetry, blood pressure) in the first 5 days.

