### **5.4 OUTCOME MEASURES**

Primary outcome:

The burden of cerebral hypoxia and hyperoxia during the first 5 days expressed as percent hours.

Exploratory secondary outcomes:

- Newborn mortality rates prior to home discharge
- Brain injury based on cerebral imaging prior to home discharge
- Neonatal morbidities (chronic lung disease, necrotizing enterocolitis, retinopathy of prematurity) prior to home discharge
- Physiological functions (observation of pulse oximetry) at 36-37 weeks PMA.
- Sleep architecture (based on sleep study) at 36-37 weeks PMA (at Westmead and Wellington sites only) including cerebral NIRS monitoring.
- Motor performance assessment (General movements assessment) during NICU stay and at 4 months corrected age follow up.
- Neuro-developmental outcomes until 5 years of age.
- Measurement of physiological functions (heart rate, pulse oximetry, blood pressure) in the first 5 days.

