## **STATISTICAL ANALYSIS**

Analysis will be conducted per-protocol using RStudio.Version(4) at a significance level of 0.05 with a two-sided alternative hypothesis. The reporting will adhere to the CONSORT guidelines.

Data cleaning: In absence of international guidelines on handling NIRS artifacts, the artifacts will be included in the data analysis. Extreme values for cerebral oxygenation (0 and 100) will be removed.

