### *Analysis of the outcomes*

Participant demographic and clinical characteristics and study outcomes will be presented using standard descriptive statistics: frequencies and percentages for categorical variables, mean, standard deviation and range or median, quartiles and range for continuous variables. All efficacy analyses will be performed according to randomized treatment. We will use a suitable transformation to ensure normality for the primary outcome, the burden of cerebral hypoxia and hyperoxia and use generalized estimating equation (GEE) or a similar method for comparison between groups. Sub-group analysis for stratification variables will be performed. For reporting the burden of cerebral hypoxia and hyperoxia, we will include deviations in cerebral oxygenation more than a minute. This pragmatic approach will ensure we achieve a balance between responding to an alarm from poor sensor contact with the participant and identifying true real-time changes in cerebral oxygenation. To allow comparison of the primary outcomes with other studies, we will also report the burden of cerebral hypoxia and hyperoxia more than 10 minutes. Other study outcomes will be compared using similar methods, using GEE methods with normal or binary outcome distribution and correlation between outcomes in twins. Adjusted models will explore predictors out outcomes. No corrections for multiple hypotheses will be performed. Adjusted models will be used to explore predictors of outcomes. Variables that differed significantly between the two groups, and could plausibly contributory to the outcome, will be considered for adjustment. A fixed adjustment for gestational age category will be included as an a priori specified variable. For this trial, no imputation of missing data will be performed and sensitivity analysis will only be performed separately for the burden of cerebral hypoxia and cerebral hyperoxia. In future, sensitivity analysis may be performed for variables such as specific gestational age or treatment received.

Withdrawn participants will be replaced in the study with new randomisation (per protocol). To facilitate and ensure long term follow up, existing measures which are standard practices includes providing appointment letters by post, reminding and confirming with families by phone and/or text message when follow up appointment is close to date.

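### Lung disease, retinopathy and neurodevelopment are compared separately from death with no death-inclusive analysis, so a survival difference could make the arm with better survival look harmed

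*Combined protocol and SAP*

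**What the plan says.** Protocol section 5.4 labels the secondary outcomes exploratory. The SAP repeats them under Secondary outcomes. Three entries matter here, each listed on its own:

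- death: "Newborn mortality rates prior to home discharge"
- morbidity: "Neonatal morbidities (chronic lung disease, necrotizing enterocolitis, retinopathy of prematurity) prior to home discharge"
- development: "Neuro-developmental outcomes until 5 years of age"

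The SAP section Analysis of the outcomes gives one sentence on method: "Other study outcomes will be compared using similar methods, using GEE methods with normal or binary outcome distribution and correlation between outcomes in twins". It adds that "no imputation of missing data will be performed". The only sensitivity analysis planned for this trial splits the primary outcome into hypoxia and hyperoxia.

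Neither document gives a denominator for these outcomes. Neither says whether a baby who dies before chronic lung disease, retinopathy or a developmental score can be assessed is excluded, counted as event-free or counted as an event. A composite with death is named only for the later large trial (protocol section 4.3).

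The analysis set is also unsettled. Under Statistical Analysis the SAP says "Analysis will be conducted per-protocol using RStudio.Version(4) at a significance level of 0.05 with a two-sided alternative hypothesis", and under Analysis of the outcomes it says "All efficacy analyses will be performed according to randomized treatment".

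**The concern.** A baby who dies early cannot go on to have chronic lung disease, late retinopathy, or a Bayley or Wechsler score. Developmental scores will therefore exist for survivors only. Followed as written, the binary morbidities will be analysed in one of two ways:

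- **Survivors only.** This conditions on an event after randomisation. If one arm keeps more fragile babies alive, and they carry a higher risk of lung or eye disease, that arm looks worse with no causal harm.
- **All babies, deaths as event-free.** This keeps the randomised groups but gives credit for deaths. The arm with more deaths has fewer babies left to be cases, so it looks better even if the risk among survivors is identical.

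The trial is meant to precede a larger one (protocol sections 4.2 and 4.3). An apparent excess of lung or eye disease that only reflects better survival could weigh wrongly in how this trial is read.

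**Working it through.** **Inputs.** The counts come from Table 1 in protocol section 4.3 (the earlier phase II trial, NIRS-guided versus control). I take its bronchopulmonary dysplasia (BPD) row as the counterpart of this trial's chronic lung disease (CLD). The plan states no power for these outcomes.

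**Step 1. Reproduce Table 1.** With risk ratio RR = (a/n1)/(b/n2) and SE(log RR) = √(1/a − 1/n1 + 1/b − 1/n2):

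| Outcome | NIRS | Control | Crude RR (95% CI) | Printed RR |
|---|---|---|---|---|
| Death | 12/86 = 14.0% | 20/80 = 25.0% | 0.56 (0.29 to 1.07) | 0.50 |
| BPD | 41/72 = 56.9% | 28/60 = 46.7% | 1.22 (0.87 to 1.71) | 1.27 |
| Retinopathy | 14/86 = 16.3% | 8/80 = 10.0% | 1.63 (0.72 to 3.67) | 1.64 |

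The percentages agree. The printed ratios may come from another model, so I do not treat the gaps as errors.

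**Step 2. Look at the denominators.** Survivors are 86 − 12 = 74 and 80 − 20 = 60. BPD uses 72 and 60, close or equal to the survivors. Retinopathy uses 86 and 80, which is all babies. Two conventions appear to sit in one table.

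**Step 3. Count deaths.**

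- Death or BPD, assuming no BPD case died: (12 + 41)/86 = 61.6% v (20 + 28)/80 = 60.0%, RR 1.03 (0.80 to 1.31). Leaving out the two unassessed NIRS-arm survivors: 53/84 = 63.1%, RR 1.05. Counting both as BPD: 55/86 = 64.0%, RR 1.07. The difference falls from +10.3 to +1.6 percentage points (first version).
- Death or retinopathy, if no baby had both: (12 + 14)/86 = 30.2% v (20 + 8)/80 = 35.0%, RR 0.86 (0.56 to 1.34). The difference moves from +6.3 to −4.8 points.

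**Step 4. Vary the overlap for retinopathy.** Table 1 does not say how many babies with retinopathy died.

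- Maximum overlap in both arms: 14/86 v 20/80, RR 0.65.
- Maximum in the NIRS arm only: 14/86 v 28/80, RR 0.163/0.350 = 0.47.
- Maximum in the control arm only: 26/86 v 20/80, RR 0.302/0.250 = 1.21.
- With no overlap in the NIRS arm, the reversal is lost once four control cases died: 26/86 = 0.302 v 24/80 = 0.300.

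The whole range, 0.47 to 1.21, lies below 1.63.

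**Step 5. Illustrate at this trial's size with no true effect on CLD.** Assumptions: 50 per arm; mortality 14% v 25% as in Table 1; every baby who would survive under control also survives under the intervention; CLD risk 47% in those babies; risk q in the extra 11% of survivors, with q assumed from 47% to 100%. Survivors number 43 v 37.5.

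| Analysis | Intervention | Control | RR, q = 47% to 100% |
|---|---|---|---|
| Survivors only | (0.75 × 0.47 + 0.11q)/0.86 | 0.47 | 1.00 to 1.14 |
| Deaths event-free | 0.75 × 0.47 + 0.11q | 0.75 × 0.47 = 0.3525 | 1.15 to 1.31 |
| Death or CLD | 0.14 + 0.75 × 0.47 + 0.11q = 54.4% to 60.3% | 0.25 + 0.3525 = 60.3% | never above 1 |

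The survivor-only ratio moves off 1 only when q differs from 47%. The event-free convention gives 1.15 even at equal risk.

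**Necrotising enterocolitis.** 9/86 = 10.5% v 10/80 = 12.5%, RR 0.84. Table 1 shows no reversal here. It also has no developmental counts, so for development the point rests on who can be assessed.

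**The case against.** - **The plan is silent, not wrong.** A reader might infer that the SAP prescribes a survivor-only analysis, or that it would report excess lung and eye disease. Neither is written. The documents support only that it could. This stands.
- **Survivor-only bias is conditional and small against the noise.** It needs the extra survivors to be at higher risk. With 43 v 37.5 survivors at 47% risk, SE(log RR) = √[(0.53/0.47)(1/43 + 1/37.5)] = 0.237. A null ratio then ranges over about 0.63 to 1.59 (ignoring twins), wider than the 1.00 to 1.14 shift. This limits the consequence but does not remove the bias.
- **Table 1 proves nothing about cause.** It describes another trial and does not label 72 and 60 as survivors. Its printed intervals for BPD (0.94 to 1.50) and retinopathy (0.75 to 3.00) include 1, and adjusted mortality has p = 0.10. It cannot separate a survival artefact from real harm. This stands.
- **The stakes are limited.** The outcomes are exploratory, mortality is listed beside them, and no rule ties the larger trial to lung or eye results. This stands.
- **A composite could hide harm.** The treatment algorithms (protocol section 6.5) include changes to inspired oxygen and airway pressure, so direct lung or eye effects are plausible. Reducing the components to description could bury such harm under fewer deaths. This stands and shapes the fix.
- **A denominator of all randomised babies is not fully available.** Protocol section 7.4 bars use of data without consent, and its subsection on parents who cannot be approached has data removed, including after a death. A composite cannot recover those deaths. This stands too.

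**Conclusion.** The point holds as a gap that could mislead. The SAP compares CLD, retinopathy and neurodevelopment apart from death, with no imputation, no stated denominator and no analysis that counts deaths. If mortality differs, either default convention could make the arm with better survival look harmed.

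In the earlier trial's counts, including deaths takes the lung ratio from 1.22 to 1.03 to 1.05, and the eye ratio from 1.63 to 0.86 if no baby had both (0.47 to 1.21 over every possible overlap). At this trial's size, under the stated assumptions and no true effect, the spurious CLD ratio is 1.00 to 1.14 among survivors and 1.15 to 1.31 with deaths as event-free.

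A reader might go further and infer that the earlier trial's excess lung and eye disease was an artefact of survival. The documents do not support that: every interval computed for these comparisons includes 1, and the table cannot distinguish the explanations. The case for change rests on the mechanism and on how little the remedy costs.

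**What to change.** In the SAP section Analysis of the outcomes, before unblinding:

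1. Add death-or-CLD, death-or-retinopathy and death-or-neurodevelopmental-impairment as prespecified companion GEE comparisons, with all randomised babies who have consented data as the denominator. State the impairment cut-off; the outcomes table in protocol section 6.5 names Bayley and Wechsler scores but no threshold.
2. Keep the between-arm comparison of each component beside its composite, so that a direct lung or eye harm is not masked. Label any survivor-only result as conditional on survival.
3. Count necrotising enterocolitis that occurs before death, over the same denominator.
4. Report by arm, where approvals permit, how many babies had data removed under protocol section 7.4 and its subsection on parents who cannot be approached.
5. Reconcile the per-protocol and as-randomised statements, so that the denominator is defined.

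Cost: SAP wording, an agreed impairment definition and a few derived variables. Mortality and morbidity data are already collected (protocol section 6.2). The small downside is that a composite mixes death with less serious events, which is why the components must be shown. This is a cheap improvement.
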